## Informed consent and screening

Patients identified by PICs that would like further information on taking part in the trial will be asked by their routine care provider to contact a member of the research team in order to register their interest in the EndoBarrier trial. A copy of the study summary will then be forwarded to patients. Participants contacting the research team as a result of advertisements/websites will be forwarded a copy of the summary PIS. If the patient would like to enter the trial, with the patient's verbal consent, a preliminary telephone screening will take place in order to check for basic inclusion and exclusion criteria. This telephone screening will follow a prepared transcript and will include only basic questions including: age, self-reported height and weight (to determine BMI), date of type 2 diabetes diagnoses and current drug therapies (to exclude patients with insulin controlled type 2 diabetes or NSAID requirements) and history of GI surgery or bleeding. Written consent will be obtained from the patient to contact their GP in order to gain further details on the patient's medical history, current medical therapies and to identify any medical reasons why the patient should not take part. At Southampton, patient's written consent will also be obtained to access the Hampshire Health Record (HHR) which contains patient information extracted from GPs and Hospital records. This information will be available to all clinical research staff at Southampton. A copy of the full PIS will be sent to the patient before the screening visit.

Patients who appear to meet eligibility criteria following their telephone screening and on review of their GP feedback, will be invited to attend a screening visit.

Patients will be informed of the nature of the study and given relevant information about the objectives of the research, benefits and possible adverse events, verbally and in writing. They will also be asked to participate in one of the three sub-groups of the mechanistic research part of the study. The methods and potential risks to which participants will be exposed to will be explained to them. Participants will have the opportunity to ask any questions and will be informed of their right to withdraw from the study at any time, without incurring any repercussions. Participants will be given as much time as is required to consider their participation in the study. Study procedures will be performed only once the participant has given full written informed consent and satisfies all the inclusion/exclusion criteria. It must be stated in the medical record that the subject is participating in the current trial.

After obtaining informed consent at the screening visit, subject's eligibility will be further assessed and documented by using a questionnaire with a list of inclusion and exclusion criteria, medical history (including all medications past and current) will be acquired and the following measurements will be performed: body weight, height, waist circumference, blood pressure, ECG, urine dipstick and pregnancy test, blood parameters (see 5.5.10) and female patients will be asked to report the last day of their menstrual period, the length of their cycle and the length of their menstruation (bleeding). This information will be used to ensure they are not pregnant and it will also help to monitor any changes in their menstrual cycle during the course of the study. Patient demographics will also be collected. At the screening visit, patients will be given the opportunity to consent for participation in one of the mechanistic sub-groups (1-3) of this study. Following informed consent, patients interested in consenting for participation in Sub-group 1 of the study will also be screened for suitability by checking the patient does not self-report to be vegetarian,

|                                                                                   |                                                                                                  |                                           |                                                             |                                                  |
|-----------------------------------------------------------------------------------|--------------------------------------------------------------------------------------------------|-------------------------------------------|-------------------------------------------------------------|--------------------------------------------------|
| [figure not shown] | Title:
EndoBarrier TM
Gastrointestinal Liner
Diabetes Trial | Protocol No:
Version 5.0 | Sponsor:
Imperial College
London | Date:
5th March 2018 |
|-----------------------------------------------------------------------------------|--------------------------------------------------------------------------------------------------|-------------------------------------------|-------------------------------------------------------------|--------------------------------------------------|

vegan, gluten or lactose intolerant (to be recorded in the CRF). They will also be checked for their fMRI suitability using these questionnaires:

- (i) Metal check form - to ensure safety for MRI scanning, as may preclude entry into fMRI study
- (ii) Handedness Inventory - inability to use a right-handed button pad will preclude entry into fMRI study using Handedness.

## 5.2 Randomisation

After the screening visit, all eligible patients for the trial will be randomised into one of the two arms of the study via the InForm system (the eCRF database for the study) which will be programmed with a randomisation schedule provided by an independent statistician. This will protect against bias in the randomisation process as patients are allocated automatically. The randomisation will be stratified by site and two BMI groups, 30-40 and 40-50 kg/m^2. The subjects will be informed about their allocated treatment arm on visit 2.

Only the subject number and subject initials will be recorded in the case report form, and if the subjects name appears on any other document (e.g. pathologist report) it will be completely anonymised. The investigator will maintain a personal subject identification list (subject numbers with the corresponding subject names) to enable records to be identified.

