## 5.4 Visit procedures

### Visit 1 – Screening visit

The following will be performed:

- Informed consent (5.1)
- Inclusion and exclusion criteria (4.2, 4.3)
- Demographics (5.1)
- Medical history including diseases, disorders and medication (5.1)
- Physical examination (5.5.4)
- Body measurements including height, weight and waist circumference (5.5.8, 5.5.9)
- Vital signs (5.5.7)
- ECG (5.5.5)
- Routine haematology and biochemistry (5.5.10)
- Metal check form (sub-group 1 only) (5.1)
- Handedness questionnaire (sub-group 1 only) (5.1)
- Urine dipstick and female pregnancy test (females) (5.5.6)
- Registration on screening log (5.1)

Once all data including blood test results related to the screening have been obtained, the Investigator will review the subject's eligibility to continue in the trial. If the subject is eligible after this review, subject will be randomised into one of the two study arms (using InForm eCRF).

### Visit 2

The following will be performed:

- Body measurements including weight and waist circumference (5.5.8, 5.5.9)
- Vital signs (5.5.7)
- Adverse events (6)
- Medical history/medication changes (5.5.4)
- Advised of randomisation into either the EndoBarrier (treatment) group or standard care (control) group (5.1)
- H. Pylori test (5.5.16)
- Dietary counselling with dietitian (see 5.5.3)
- Preparation with gastroenterologist for EndoBarrier Implant (Treatment arm only) (5.5.2) – including distribution of proton pump inhibitors.
- Diabetologist/Endocrinologist (5.5.1)

|                                                                                   |                                                                                                  |                                           |                                                             |                                                  |
|-----------------------------------------------------------------------------------|--------------------------------------------------------------------------------------------------|-------------------------------------------|-------------------------------------------------------------|--------------------------------------------------|
| [figure not shown] | Title:
EndoBarrier TM
Gastrointestinal Liner
Diabetes Trial | Protocol No:
Version 5.0 | Sponsor:
Imperial College
London | Date:
5th March 2018 |

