### **Visit 3, 5, 8, 10, and 14**

The following will be performed:

- Body measurements including weight and waist circumference (5.5.8, 5.5.9)
- Vital signs (5.5.7)
- Routine chemistry and haematology (5.5.10)
- Urine albumin-creatinine ratio (5.5.11)
- Adverse events (6)
- Medical history/medication changes (5.5.4)
- Health economics questionnaires (EQ-5D-5L and service use) (5.5.4)
- Collection of blood for DNA & RNA (5.5.13)
- Metabolomics protocol (5.5.14)
- Bioelectrical impedance analysis (5.5.15)
- Functional MRI protocol except visit 5, 10 and 14 (sub-group 1) (5.6.8)
- Fasting gut hormones and metabolites (sub-group 1-3) (5.6.4)
- Post meal gut hormones and metabolites (sub-group 1 and 3) (5.6.4)
- Eating and behaviour questionnaires except visit 5 (sub-group 1-3) (5.6.1)
- Insulin clamp protocol except visit 10 and 14 (sub-group 2) (5.6.10)
- Taste and food preference protocol except visit 10 and 14 (sub-group 3) (5.6.11)
- Eating behaviour computerised tasks except visit 5 (sub-group 1 and 3) (5.6.5)
- Cognitive assessment tasks except visit 5 and 14 (sub-group 1) (5.6.9)
- Food diaries (sub-groups 1-3) (5.6.2)
- Appetite visual analogue scales (sub-groups 1-3) (5.6.3)
- DS-R Disgust questionnaire visit 3 only (sub-group 1) (5.6.6)
- 24hr Dietary Recall sub-group 3 only (5.6.11)

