### 5.5.12 Health Economics Questionnaires

Patients in both treatment arms will be asked to complete the health economics questionnaires at visits 3, 5, 7, 8, 10 and 14. These comprise the EQ-5D-5L questionnaire (<http://www.euroqol.org/eq-5d-products/how-to-obtain-eq-5d.html>) to assess health-related quality of life, and a bespoke questionnaire designed to collect information about patients' use of health and social care resources (for costing purposes).

The resource use questionnaire will be adapted from existing instruments including the CONSTRUCT (Williams J G, Russell I, Cohen D, et al. Comparison of infliximab and ciclosporin in steroid resistant ulcerative colitis: a trial CONSTRUCT, NIHR Health Technology Assessment

|                                                                                   |                                                                                                  |                                           |                                                             |                                                  |
|-----------------------------------------------------------------------------------|--------------------------------------------------------------------------------------------------|-------------------------------------------|-------------------------------------------------------------|--------------------------------------------------|
| [figure not shown] | Title:
EndoBarrier TM
Gastrointestinal Liner
Diabetes Trial | Protocol No:
Version 5.0 | Sponsor:
Imperial College
London | Date:
5th March 2018 |
|-----------------------------------------------------------------------------------|--------------------------------------------------------------------------------------------------|-------------------------------------------|-------------------------------------------------------------|--------------------------------------------------|

programme, <http://www.hta.ac.uk/project/1737.asp>;

<http://www.dirum.org/instruments/details/27>) and Chernak (Chernyak et al. BMC Health Services Research 2012, 12:303, <http://www.biomedcentral.com/1472-6963/12/303>) questionnaires and will ask patients to specify what services they have used since the previous assessment. The resource use questionnaire will include:

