### 5.6 Sub-group specific procedures and measurements

#### 5.6.1 Eating and Behaviour Questionnaires (sub-groups 1-3)

At Visits 3, 8, 10, 14 patients will complete eating and behavioural questionnaires (duration 60 minutes) to assess eating behaviour and attitudes and personality measures related to reward sensitivity and mood. If they do not manage to complete all the questionnaires in the time available they will be able to complete them at home using pen and paper or over the internet.

1. EPIC food frequency Questionnaire
2. Dutch Eating Behaviour Questionnaire (DEBQ) – to measure restraint, emotional and external influences on eating behaviour
3. Eating Disorder Examination Questionnaire (EDE-Q) – to screen for existing eating disorder and binge eating
4. Behavioural Inhibition and Activation System (BIS / BAS) scales – to measure punishment and reward sensitivity
5. Beck Depression Inventory (BDI-II) – to measure to measure levels of depression and anxiety
6. Barratt Impulsivity Scale and UPPS-P – to measure impulsivity

|                                                                                   |                                                                                                  |                                           |                                                             |                                                  |
|-----------------------------------------------------------------------------------|--------------------------------------------------------------------------------------------------|-------------------------------------------|-------------------------------------------------------------|--------------------------------------------------|
| [figure not shown] | Title:
EndoBarrier TM
Gastrointestinal Liner
Diabetes Trial | Protocol No:
Version 5.0 | Sponsor:
Imperial College
London | Date:
5th March 2018 |
|-----------------------------------------------------------------------------------|--------------------------------------------------------------------------------------------------|-------------------------------------------|-------------------------------------------------------------|--------------------------------------------------|

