
Patient-level cost and QALY estimates will be combined to estimate an Incremental Cost Effectiveness Ratio (ICER) for the Endobarrier device compared with standard medical therapy over the 24 month trial period. The analysis will combine multiple imputation to account for missing EQ-5D and resource use data with bootstrap regression to estimate mean cost and QALYs for the two patient groups. Missing data is often a particular problem for economic analysis, even in studies with good follow-up of primary endpoints, as area under the curve approach requires data from multiple time points. A bootstrap regression approach will be used to account for non-normal distributions of cost data, to adjust for baseline differences in utility or other patient characteristics, and to allow for correlations between costs and QALYs.

**Cost-effectiveness modelling:** A decision analytic model will be developed to estimate clinical outcomes, QALYs, and costs beyond 24 months. The time horizon for the modelling will be for the remainder of the patient's predicted lifetimes, as recommended in modelling guidelines.

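### Patients learn their arm at Visit 2, but the first EQ-5D-5L and the first eating, mood and quality-of-life questionnaires come at Visit 3, so these self-reported baselines are open to an allocation effect

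*Protocol*

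**What the plan says.** **Allocation and disclosure.** Randomisation follows the eligibility review after screening. Section 5.4 (Visit 1) says: "If the subject is eligible after this review, subject will be randomised into one of the two study arms". Section 5.2 then says: "The subjects will be informed about their allocated treatment arm on visit 2". The Visit 2 list in section 5.4 agrees. Table 2 puts Visit 2 at week -4 and Visit 3 at week -2, each with a window of 7 days either way.

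**First self-reports.** Section 5.5.12: "Patients in both treatment arms will be asked to complete the health economics questionnaires at visits 3, 5, 7, 8, 10 and 14". Table 2 also marks Visit 6, but both have Visit 3 as the first occasion. For sub-groups 1-3, section 5.6.1 says: "At Visits 3, 8, 10, 14 patients will complete eating and behavioural questionnaires". That battery includes BDI-II, HADS, PANAS and SF36. Neither set is scheduled at Visit 1 or 2.

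**Use in the analysis.** Under Health Economics, section 8.2 takes the week -2 EQ-5D as its first utility and uses bootstrap regression, among other purposes, "to adjust for baseline differences in utility or other patient characteristics". For food hedonics and questionnaires, section 8.2 uses a two-by-two ANOVA with group, time from baseline to follow-up, and their interaction.

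**Masking.** Section 3.1 compares the device with standard medical therapy and describes neither blinding nor a sham. Section 1.6 does call the trial placebo-controlled, but nothing in the design matches that word.

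**The concern.** A baseline covariate is safe to adjust for because allocation cannot have changed it. Here it can have. By Visit 3 a patient has normally known the arm for about two weeks and may feel hopeful or disappointed. The input received also differs by arm: at Visit 2 the device arm sees the gastroenterologist and gets written advice on eating after insertion (sections 5.4 and 5.5.3). Randomisation does not balance a difference that arises after disclosure.

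Two results are at stake. One is the baseline-adjusted QALY difference, and with it the incremental cost per QALY, which section 2.5 lists as a secondary endpoint. The other is the set of group-by-time tests on the questionnaires.

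**Working it through.** The plan gives no figure on this point to reproduce. The sample size rests on HbA1c response rates and is not involved.

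**1. Order of events (Table 2, section 5.4).** Visit 2 is at day -28 ± 7 and Visit 3 at day -14 ± 7.
- Nominal interval: 28 - 14 = 14 days.
- Shortest: Visit 2 at day -21, Visit 3 at day -21, so 0 days.
- Longest: Visit 2 at day -35, Visit 3 at day -7, so 28 days.

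On the nominal schedule every EQ-5D and section 5.6.1 baseline follows disclosure.

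**2. Which baselines are exposed**

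| Measure | First taken | Relative to disclosure | Patients |
|---|---|---|---|
| HbA1c (Table 4) | Visit 1; next at Visit 5 | before | all |
| Weight, waist, blood pressure | Visit 1 | before | all |
| EQ-5D-5L | Visit 3 | after | all |
| Section 5.6.1 questionnaires | Visit 3 | after | optional sub-groups |

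**3. Effect on the adjusted QALY difference.** Let *d* be the between-arm gap in Visit 3 utility caused by disclosure, *b* the slope of later utility on baseline utility, and *T* the time covered. If the gap is transient, adjustment moves the QALY difference by about *b* × *d* × *T* against the arm whose baseline was raised.
- *T*, from week -2 to month 23: 23/12 + 14/365.25 = 1.955, about 1.96 years.
- *d* and *b* are not in the documents. Assumed: *d* from 0 to 0.05, *b* from 0.5 to 0.7.

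| *d* | *b* = 0.5 | *b* = 0.7 |
|---|---|---|
| 0 | 0 | 0 |
| 0.02 | 0.020 | 0.027 |
| 0.05 | 0.049 | 0.069 |

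The raised baseline also adds to that arm's own area under the curve, but it carries weight only over the 24 days from day -14 to day +10: 0.5 × 24/365.25 = 0.033 years. At *d* = 0.05 this offsets 0.0016 QALY. With *b* widened to 0.4-0.8, the shift at *d* = 0.05, net of the offset, is 0.038 to 0.077.

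**4. Effect on group-by-time.** The interaction is (follow-up - baseline) in the device arm minus the same in controls. A disclosure gap *d* at baseline that does not persist enters it in full, as -*d*.

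**The case against.** Several objections have force.

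- **The bias is possible, not shown.** A reader might infer that the baselines are contaminated and that every questionnaire interaction is biased. The documents show exposure only. Section 5.6.1 also contains personality, smoking and alcohol scales, and there is no particular reason to think that learning the arm moves those.
- **The magnitude is assumed.** The gap could be zero, and a slope held constant for two years is a simplification.
- **The consequence is limited.** A reader might extend the point to the main result. Table 4 rules that out: the only HbA1c before treatment is at Visit 1, before randomisation, and it is a laboratory value.
- **One earlier mood score may exist.** Exclusion criterion 15 uses a BDI-II cut-off, which implies a score before randomisation, although no visit lists one.
- **Home completion is not a general option.** Section 5.6.1 says of patients who run out of time that "they will be able to complete them at home using pen and paper or over the internet". This is a fallback for unfinished forms and does not by itself show that the battery can be done before Visit 2.
- **Not everything can move.** Section 5.6.3 ties the appetite scales to the meal sampling periods, and section 5.6.8 plans to correlate scans with questionnaires and test meals.
- **An earlier baseline has uneven timing.** Under section 5.5.16, device-arm patients who test positive for H. pylori have one week of treatment, are retested four weeks later and repeat Visit 2.
- **The trial was already running.** Section 7.2 deals with patients who withdrew under version 4.1.

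These narrow the scope and shape the remedy. None changes the visit order or the use of the Visit 3 values as baseline.

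**Conclusion.** The point holds in a limited form. The self-reported baselines (EQ-5D-5L for everyone, the section 5.6.1 battery for the sub-groups) are scheduled after patients know their arm, and section 8.2 relies on them for QALY adjustment and group-by-time tests. Both results are open to bias of unknown size. The illustrative 0 to about 0.07 QALY rests on an assumed gap of 0 to 0.05, an assumed constant slope of 0.5 to 0.7, and a disclosure effect that fades after Visit 3. The documents give no expected QALY difference, so the effect on the ICER cannot be sized. The primary endpoint and the sample size are untouched. This is a cheap improvement to a secondary analysis, not a flaw in the main comparison.

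**What to change.** **Patients not yet told their arm.** Have EQ-5D-5L and the section 5.6.1 questionnaires completed at the start of the first Visit 2, before disclosure, and use these as baseline. Label any form finished after disclosure as such. Leave appetite scales, test meals, fMRI and clamps at Visit 3 and state that their baselines are post-disclosure. If a BDI-II is done for eligibility, list it in the visit schedule.

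**Patients already past Visit 2.** Label the Visit 3 values as post-disclosure. Report QALY and ICER results with and without adjustment for baseline utility. Report questionnaire results both as change from baseline and as a between-arm comparison of follow-up values. If nobody remains to be told, this is the whole fix.

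**Cost.** There is no new assessment. A short EQ-5D, and for sub-group patients about 60 minutes of questionnaires (the duration in section 5.6.1), move from Visit 3 to Visit 2. The baseline becomes about two weeks older, and about five weeks older again for H. pylori-positive device patients who repeat Visit 2 (1 + 4 weeks), so this delay falls in one arm only. Questionnaires would no longer be taken on the same day as the scans and meal tests, which weakens the planned baseline correlations. If both timings end up in use, the analysis must identify which baseline each patient has. One gain is that patients who leave between Visits 2 and 3 would still have a baseline.
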